## Abstract

**Introduction:**

Loneliness and social isolation have been identified as significant public health concerns, but improving relationships and increasing social participation may improve health outcomes and quality of life. The aim of the Project About Loneliness and Social networks (PALS) study is to assess the effectiveness and cost-effectiveness of a guided social network intervention within a community setting among individuals experiencing loneliness and isolation and to understand implementation of Generating Engagement in Network Involvement (Genie) in the context of different organisations.

**Methods and analysis:**

The PALS trial will be a pragmatic, randomised controlled trial comparing participants receiving the Genie intervention to a wait-list control group. Eligible participants will be recruited from organisations working within a community setting: any adult identified as socially isolated or at-risk of loneliness and living in the community will be eligible. Genie will be delivered by trained facilitators recruited from community organisations. The primary outcome will be the difference in the SF-12 Mental Health composite scale score at 6-month follow-up between the intervention and control group using a mixed effects model (accounting for clustering within facilitators and organisation). Secondary outcomes will be loneliness, social isolation, well-being, physical health and engagement with new activities. The economic evaluation will use a cost-utility approach, and adopt a public sector perspective to include health-related resource use and costs incurred by other public services. Exploratory analysis will use a societal perspective, and explore broader measures of benefit (capability well-being). A qualitative process evaluation will explore organisational and environmental arrangements, as well as stakeholder and participant experiences of the study to understand the factors likely to influence future sustainability, implementation and scalability of using a social network intervention within this context.

**Ethics and dissemination:**

This study has received NHS ethical approval (REC reference: 18/SC/0245). The findings from PALS will be disseminated widely through peer-reviewed publications, conferences and workshops in collaboration with our community partners.

**Trial registration number:**

ISRCTN19193075

Strengths and limitations of this studyThis study will evaluate an existing social network intervention (Genie, Generating Engagement in Network Involvement) in the context of loneliness and social isolation.The Project About Loneliness and Social networks study consists of a pragmatic randomised controlled trial implemented in conjunction with community-based stakeholders in a community setting in two areas of the UK.The process evaluation and analysis has been designed to understand the factors influencing the implementation and scalability of social network interventions in this context.

## Introduction

Social isolation is considered to be an objective lack of social connections, contact or participation, while loneliness is a subjective psychological state where there is a discrepancy between desired and perceived levels of support or connectedness.^1 2^ The prevalence rates of loneliness and isolation vary;^3^ however, it is estimated to affect about 30% of the adult population in the UK.^4^ Specific at-risk groups, such as the elderly, minority communities and those with long-term mental or physical health conditions are significantly more isolated than those in good health.^3 5 6^ The Office of National Statistics (ONS) recently identified three profiles of individuals who are ‘at-risk’; these suggest that different factors may be important in the experience of loneliness at different points across the life course.^7^

### The problem: health implications of loneliness and social isolation

The impact of loneliness and isolation on well-being and the associated health risks have been identified as a significant public health concern^8 9^ exacerbated by the prevalence of long-term conditions and advancing age.^10^ Both loneliness and social isolation are associated with poor physical and mental health outcomes,^11–13^ reduced quality of life^14 15^ and is linked to poorer physiological outcomes such as raised blood pressure and increased health-risk behaviours (eg, sedentary behaviour).^16^ Their impact on mortality is estimated to exceed that of traditional risk factors such as obesity and cigarette smoking, with a 50% higher risk compared with socially integrated participants.^17–19^ There are also significant costs associated with raised demand and use of health services, and loneliness is associated with increased general practitioner (GP) appointments, emergency hospital admittance and premature social care use.^20–22^

### Social relationships and preventing or reducing loneliness and social isolation

Although the determinants of loneliness and isolation are varied, social and emotional support from others is likely to be protective,^23^ with emerging evidence suggesting that improving the quality of interpersonal relationships and participation in social activities may be key to tackling the impact of loneliness.^9^ Evidence has indicated that increasing social interactions and the number of people who can be relied on is associated with reduced levels of distress,^24^ while connecting with community resources can help protect against loneliness for those who are most at risk.^9 25^ Furthermore, there is evidence that social network interventions can significantly improve health outcomes, quality of life and increase the take-up of new activities.^26 27^ A diverse and supportive network has been shown to reduce health service costs.^28^ A recent The National Institute for Health and Care Excellence (NICE) quality standard recommends the navigation of older vulnerable people to community activities as a means of preventing loneliness in this group.^25^

### Rationale and risk benefits for the current trial

In line with this evidence, there is a logical argument for introducing an effective social network intervention outside of formal healthcare settings to connect people who are experiencing loneliness to others within their communities.^25^ Creative engagement with non-traditional informal providers of wellness management (such as through accessing locally available community groups) offers an alternative opportunity to address health and social needs. We envisage that the study will offset any burden through providing wider benefit to organisations; first through staff development and training integrating the intervention into practice, and, second, by providing a resource and alternative referral pathway for individuals who they have identified at risk of isolation or loneliness (potentially extending beyond the life of the study). A series of nestled qualitative process studies will examine the context, practices and processes relating to implementing the intervention within the community context, and an economic evaluation to assess whether this is cost-effective.

### Study aims and research questions

The aim of the Project About Loneliness and Social networks (PALS) study is to assess the feasibility, acceptability, effectiveness and cost-effectiveness of a facilitated social network intervention compared with a wait-list control within a community setting among at-risk populations, and to understand the implementation in the context of different organisations who work in this environment. The Genie (Generating Engagement in Network Involvement) intervention is an online, facilitated, social networking tool designed to develop opportunities for social involvement.

Primary objectivesTo determine the effect of Genie compared with usual care on mental health (SF-12 composite scale score) at 3 and 6 months.

Secondary objectivesTo determine the effect of Genie compared with usual care on loneliness, social isolation, physical health and engagement with new activities at 3 and 6 months.To establish whether the use of Genie within a community setting is cost-effective.

Process analysis objectivesTo assess the acceptability and feasibility of running the study based on recruitment and retention during an internal pilot phase.To explore the experiences of using Genie, how the intervention impacts on loneliness and isolation and the mechanisms by which participants enact change.To explore contextual environmental and organisational factors that inhibit or promote the integration, sustainability and scalability of Genie for addressing loneliness in local and organisational settings.

## Methods and analysis

### Study design and setting

We will conduct a pragmatic, randomised controlled trial comparing participants receiving the facilitated social network Genie intervention to a wait-list control group; randomisation will be at individual and/or cluster (facilitator) level (see Randomisation section). We will work closely with community partners two localities (centred around Southampton and Liverpool) in identifying participants and delivering the intervention, as well as informing our understanding of the challenges and environmental factors associated with implementation. Partners may include any group or organisation that has the potential to identify or access at-risk individuals.

### Study participants

#### Identification

We will use a multistranded recruitment strategy to reflect the diversity of individuals who are living with loneliness or in isolation. This will be facilitated by collaborating community organisations to ensure that we are able to identify and access those most at-risk. Potential participants will be identified in the manner that best operates within existing working practices for each organisation (which will be different for each organisation/collaborator). This is necessary to explore the integration and scalability of Genie in local and organisational settings. Potential participants will be invited by the organisation; this may be by letter or during routine visits, appointments, or in line with the usual working practices of the partner organisation. This may include (but is not limited to) new referrals, waiting lists or opportunistic contacts during routine work of partner organisation. All eligible participants will be given a research pack including an invitation letter, participant information sheet and freepost reply slip to return should they wish to take part in the trial.

#### Eligibility criteria

We will recruit any adult (aged 18 or over) who is identified as being isolated or at risk of loneliness. We define a socially isolated person as one for whom there is an ‘absence of social contacts or community involvement, or lack of access to services’ in line with the definition used by Hampshire County Council.^29^

#### Exclusion criteria

Exclusion criteria will include participants who arecurrently hospitalised (ie, not self-managing within a community setting),those in the end stages of life or any condition which impacts on ability to take part,those lacking sufficient capacityand those having previously used the Genie intervention.

Eligibility will be assessed by the community partners and confirmed by the research team in all cases.

### Randomisation

To overcome potential issues of contamination (where a facilitator could become familiar with how GENIE works and thus find out about local activities and advise control group participants), facilitators will be 1:1 randomised to either the intervention or control arm. Randomisation will be stratified by organisation in blocks of two (ie, one facilitator will be randomised to the intervention arm and one to the control arm) and carried out by the trial statistician (SE) using the statistical software R v3.5.1. In some organisations, the risk of contamination does not exist (eg, where the only contact between a facilitator and participants would be by delivering the intervention). In these cases, some efficiency is gained by randomising the participants individually (block randomised 1:1 to intervention and control, again stratifying by organisation). The summary below details the different scenarios. Preferred options (A&B) to be used whenever possible: Randomise facilitators and participantsIntervention facilitators only to be trained

If there are organisational or setting constraints which prohibit facilitator or participant randomisation (eg, the facilitator works within a specified geographic location) we will assess whether there is ongoing contact between the facilitator and potential participants. In these scenarios: Where there is ongoing contact (C)Train intervention facilitators onlyRandomise facilitators onlyParticipants within each area allocated to facilitator (not randomised)Where there is no ongoing contact (D)Train all facilitatorsRandomise participants

**Table 1 T1:** The factors affecting the recruitment and randomisation process

Participant recruitment	Contact between participant and facilitator	
	Ongoing	One-off contact (at facilitation)
Area/location not restricted	MODEL B Randomise facilitators and participants Intervention facilitators only to be trained	MODEL A Randomise facilitators and participants Intervention facilitators only to be trained
Within a specific geographical (or other prespecified) area	MODEL C Train intervention facilitators only Randomise facilitators only Participants within each area allocated to facilitator (not randomised)	MODEL D Train all facilitators Randomise participants

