### Participant flow through the study

Written informed consent will be collected from all participants and baseline data collected with a research team member (online or on paper, dependent on the participant preferences). Allocation will occur once the baseline assessment has been completed. Participants who are allocated to the intervention condition will be given access to the Genie intervention within 2 weeks of the baseline appointment; this process will be guided by the facilitator at a location to suit them (ie, at home or in the community). At 3 and 6 months after enrolment into the study, participants will be invited to complete follow-up assessments. All follow-up assessments will be recorded no earlier than 2 weeks before the follow-up date and no later than 6 weeks after the follow-up date. Each participant will be sent a £10 high street gift voucher with the 6-month follow-up questionnaire. Individuals allocated to the control group will be offered access to Genie with the facilitator after the have completed their 6-month follow-up assessment. Participant flow is outlined in figure 1.

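### Under Model C a participant's arm follows the area's randomised facilitator, so the unqualified statement that allocation comes after baseline probably fails there and recruitment could depend on arm

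*Protocol article*

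**What the plan says.** The Randomisation section and Table 1 of the protocol article describe four models. Participants are randomised in Models A, B and D. Model C is for settings where constraints such as a fixed geographic patch rule out the preferred options and the facilitator has ongoing contact with potential participants. Its rule is: "Train intervention facilitators onlyRandomise facilitators onlyParticipants within each area allocated to facilitator (not randomised". Facilitators are randomised in pairs: "Randomisation will be stratified by organisation in blocks of two (ie, one facilitator will be randomised to the intervention arm and one to the control".

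Participant flow through the study then says, with no exception by model: "Allocation will occur once the baseline assessment has been completed". It adds that intervention participants "will be given access to the Genie intervention within 2 weeks of the baseline appointment".

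On recruitment, Identification says: "Potential participants will be invited by the organisation; this may be by letter or during routine visits, appointments", and the sources may include "new referrals, waiting lists or opportunistic contacts during routine work of partner organisation". Under Exclusion criteria: "Eligibility will be assessed by the community partners and confirmed by the research team in all cases". Eligibility itself rests on being judged isolated or at risk of loneliness; the article gives no score threshold.

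**The concern.** In Model C there is no separate step that allocates the participant. Once a facilitator is randomised, everyone in that area has an arm. The sentence on allocation after baseline therefore assures readers of concealment that Model C probably does not deliver.

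If the arm is known where people are identified and approached, those put forward can differ between arms. One arm might favour people who look ready to join activities while the other takes anyone eligible, and willingness to consent may also depend on the arm on offer. Randomising facilitators does not protect against this, because the selection happens afterwards. A larger sample does not remove it, and the primary model's only named covariate, baseline SF-12, cannot capture traits such as motivation. The same model pools Model C with individually randomised participants.

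**Working it through.** **1. Can both statements hold?** The allocation sentence is true for a Model C participant only if that person's baseline precedes the randomisation of the area's facilitator. For it to be true of all of them, the whole area must be recruited and assessed first. Four statements in the article bear on this:

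- Sources include new referrals and opportunistic contacts (Identification), so people arrive over time.
- The plan assumes 12 participants per facilitator (Sample size consideration), so about 24 per pair.
- Genie access is due within 2 weeks of each person's own baseline (Participant flow).
- Only intervention facilitators are trained (Randomisation), so facilitators know their arm once training takes place.

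A trained facilitator must therefore be in place while recruitment continues, unless about 24 people per pair can all be assessed within roughly 2 weeks. The article does not say that this is intended. The order is an inference, but a strong one.

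**2. The plan's own figures.** Inputs from Sample size consideration: difference 4, SD 10.4, 80% power, 5% type I error (taken as two-sided; the article does not say), ICC 0.05, 12 per facilitator, 15% drop-out.

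- Per arm, by t-test: 107.09, rounded up to 108, so 216 in total.
- Design effect: 1 + (12 − 1) × 0.05 = 1.55, and 216 × 1.55 = 334.8, so 335.
- 335 / 0.85 = 394.1, stated as 394.

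These reproduce and are not in dispute.

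**3. Standard error implied by the plan.** SE = 10.4 × √(2/108) = 1.415 points. This ignores any precision gained from baseline adjustment.

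**4. Illustrative bias.** Let p be the share of participants in Model C and b the difference between arms in expected 6-month score that baseline SF-12 does not remove. The bias in the pooled estimate is then about B = p × b. Neither p nor b is in the article. As an assumption, take b at 0.1 to 0.2 SD, that is 1.04 to 2.08 points, rounded to 1 and 2 below.

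False-positive rate = 1 − Φ(1.96 − B/SE) + Φ(−1.96 − B/SE).

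| p | b | B | B / 4 | B / SE | False-positive rate |
|---|---|---|---|---|---|
| 0.25 | 1 | 0.25 | 6% | 0.18 | 5.4% |
| 0.5 | 2 | 1.0 | 25% | 0.71 | 10.9% |
| 1 | 2 | 2.0 | 50% | 1.41 | 29.3% |

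If the bias runs against Genie, power to detect 4 points is Φ((4 − B)/SE − 1.96): 75.5% at B = 0.25 and 56.3% at B = 1.

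**The case against.** The article never dates facilitator randomisation, the flow diagram is not reproduced in the text at hand, and the full protocol is not shown. A reader might infer that the allocation sentence is simply false for Model C, or that everyone involved knows the arm before recruitment. The documents do not go that far. The sentence would hold if an area were fully assessed before its facilitator was randomised, and only the facilitator's own knowledge follows from the training rule. What stands is that the article does not describe that order and that its other arrangements make it impractical.

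A reader might also infer that the trained facilitator chooses whom to invite. The article assigns invitation to the organisation and eligibility to community partners; it does not name facilitators. Ongoing contact in Model C makes a role for them plausible, no more.

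There are real safeguards. All eligible people are to receive a research pack, the research team confirms every eligibility decision, and baseline is collected with a research team member. Controls are offered Genie after 6 months, which may weaken arm-dependent consent. A forest plot of effects by organisation gives some view of Model C organisations. These reduce the risk, but confirmation covers only those put forward and cannot show who was never identified.

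Blocks of two add little. They reveal the paired facilitator's arm, but training already makes each facilitator's own arm evident.

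Model C is a disclosed fallback, adopted to limit contamination, and A and B are to be used whenever possible. Its share may be small.

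**Conclusion.** The point holds as an inconsistency between the allocation statement in Participant flow and the Model C rule in Randomisation and Table 1, with a consequent risk of arm-dependent recruitment limited to Model C. It rests on one inference, that facilitator randomisation normally precedes most Model C recruitment.

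The size cannot be established. On the stated assumptions it runs from negligible (0.25 points, 5.4%) to material (1 point, a quarter of the target, about 11%). It is tempting to conclude that bias could reach half the 4-point target with a 29% false-positive rate. With a shift of at most 0.2 SD, that needs p = 2 / 2.08 = 0.96, nearly the whole trial in Model C, contrary to the stated preference for A and B. The article does not support that as an expected case. The inconsistency needs correcting whatever the size.

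**What to change.** 1. In Participant flow, limit the sentence on allocation after baseline to participants randomised individually. State that in Model C allocation is set by facilitator randomisation, and when that takes place relative to recruitment.
2. In Model C, where feasible, fix the list of eligible people in both areas of a facilitator pair before that pair is randomised, and have the research team issue invitations from it. For later referrals, have someone unaware of the facilitator's arm screen and invite.
3. Report baseline characteristics by arm within Model C, and pre-specify a sensitivity analysis of the primary outcome that excludes Model C participants.

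Recruiting in batches before randomisation should not be the main remedy. A pair is randomised once, so only the first batch is protected, and holding a batch back may conflict with the 2-week access window.

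The cost is some administrative work, a possible delay to training in Model C organisations, and a less precise sensitivity estimate. If the design effect is unchanged, its standard error is 1.415 / √(1 − p): about 1.63 points with a quarter of participants in Model C and about 2.00 with half. No extra participants are needed.

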### Participant flow through the study

Written informed consent will be collected from all participants and baseline data collected with a research team member (online or on paper, dependent on the participant preferences). Allocation will occur once the baseline assessment has been completed. Participants who are allocated to the intervention condition will be given access to the Genie intervention within 2 weeks of the baseline appointment; this process will be guided by the facilitator at a location to suit them (ie, at home or in the community). At 3 and 6 months after enrolment into the study, participants will be invited to complete follow-up assessments. All follow-up assessments will be recorded no earlier than 2 weeks before the follow-up date and no later than 6 weeks after the follow-up date. Each participant will be sent a £10 high street gift voucher with the 6-month follow-up questionnaire. Individuals allocated to the control group will be offered access to Genie with the facilitator after the have completed their 6-month follow-up assessment. Participant flow is outlined in figure 1.

